#### **4.4.3. Modified Intent-to-Treat (mITT) Set**

All randomized patients having received at least one dose of the prescription of study drug (either nangibotide or placebo). Patients will be assigned to the treatment group as randomized (i.e. with study drug assignments designated according to initial randomization, regardless of whether patients received what was assigned). The mITT Set will be considered as the primary set for interim and final efficacy analyses.

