## 8.2. Analysis of Mortality at Day 28 (ACM28)

All-Cause Mortality will be assessed using survival status up to study day 31, i.e. any death occurring between the start of study drug infusion and the start of study drug infusion + 30 days.

The number and percentage of patient alive, dead and lost to follow-up at Day 28 will be summarized by treatment group. Any patient with last date known to be alive < Day 28 without death information will be considered lost to follow-up in this summary.

Last known date to be alive will be derived using the following information:

- Death date
- If death date is not documented take the maximum of the following dates:
  - 'Date last known to be alive' documented by the investigator
  - Last patient subject visit date including date of documented follow-up clinical status planned at Day 28 and Day 60
- If derived last known alive date still isn't populated the maximum of the following can be considered:
  - Date of laboratory samples
  - Date of end of organ support
  - Date of end of follow-up, only if reason is completed
  - End date of any adverse events

Inferential analysis will be based on patients which status (alive or dead) is known at Day 28 (i.e. excluding patient lost to follow-up before Day 28). Missing data will not be imputed.

Mortality rate at Day 28 will be compared between treatment group using a CMH adjusted for baseline clinical status (5 vs 6). The common difference in mortality rates between nangibotide and placebo (nangibotide ACM28 rate - placebo ACM28 rate) will be estimated with its 95% confidence interval using the Mantel-Haenszel method. Hence, a negative difference in ACM28 rates favors nangibotide.

This analysis will be done as well according to the baseline sTREM-1 level (above or equal to the median vs below).

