### **Sensitivity analysis :**

- 1) The mortality rate at Day 28 will be compared between treatment group using a CMH adjusted for baseline clinical status (5 vs 6) and randomization stage (part 1 stage 1, part 1 stage 2 and part 2). The adjusted difference in mortality rates between nangibotide and placebo (nangibotide ACM28 rate - placebo ACM28 rate) will be estimated with its 95% confidence interval using Mantel-Haenszel method.

- 2) Kaplan-Meier estimates of mortality will also be estimated at Day 28. The same analysis will be conducted in patients with a sTREM-1 above vs below the median value at baseline.
- 3) The same analyses mentioned above (including sensitivity analyses) will be performed at Day 60.

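### The fallback dates for last known alive are effectively never reached in dosed patients, so a patient with dated evidence of life on or after Day 28 can be excluded from the Day 28 mortality test as lost

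*SAP*

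**What the plan says.** SAP section 8.2 sets the last known alive date in three steps.

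1. If there is a death date, use it.
2. If not, take the maximum of two sources: the date last known alive that the investigator documents, and "Last patient subject visit date including date of documented follow-up clinical status planned at Day 28 and Day 60".
3. Four further sources follow: laboratory samples, end of organ support, end of follow-up where the reason is completion, and adverse-event end. They are introduced by "If derived last known alive date still isn't populated the maximum of the following can be considered".

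The date then decides who is analysed: "Any patient with last date known to be alive < Day 28 without death information will be considered lost to follow-up in this summary". The test follows that classification: "Inferential analysis will be based on patients which status (alive or dead) is known at Day 28", with the gloss "i.e. excluding patient lost to follow-up before Day 28). Missing data will not be imputed".

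Efficacy is analysed in the mITT set (section 4.4.3): "All randomized patients having received at least one dose of the prescription of study drug (either nangibotide or placebo". In the schedule of procedures (section 11.1), Day 1 is the calendar day of first dosing. Clinical status is assessed before that dose, daily to Day 14, and again at Day 28 and Day 60.

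**The concern.** Step 3 is tied to an empty result from step 2, not to whether that result is the latest evidence of life. A dosed patient has at least a Day 1 visit date, so step 2 always returns something and the four further sources have no effect. Even where step 3 could apply, its wording makes the use of those sources optional.

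The error runs in one direction within an arm. Documented deaths are always counted, whereas a patient shown to be alive by a later laboratory, organ-support, end-of-follow-up or adverse-event record can be dropped. Each such exclusion shrinks the denominator and leaves the number of deaths unchanged, so the arm's mortality rate can only rise. All-cause mortality at Day 28 is the key secondary endpoint of part 2 (section 3.3.1).

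**Working it through.** The SAP gives no figure for this point, so there is nothing to reproduce. The check has two parts.

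**Logic of the rule.** The rule as written was compared with a single maximum over all dated sources, for patients with no death date (study days):

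| Investigator date | Last visit or contact | Other dated record | Rule as written | Single maximum |
|---|---|---|---|---|
| none | 14 | AE end, 33 | 14: lost | 33: alive |
| 33 | 14 | AE end, 33 | 33: alive | 33: alive |
| none | 60 (Day 28 missed) | AE end, 33 | 60: alive | 60: alive |
| none | 1 | laboratory, 30 | 1: lost | 30: alive |
| none | none | laboratory, 30 | 30: alive | 30: alive |

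Only the last row activates step 3, and it needs a patient with no visit date at all, which dosing on Day 1 effectively rules out in the mITT set. Rows 1 and 4 show the gap. It needs all of the following:
- no visit, telephone or status contact on or after Day 28
- no investigator date on or after Day 28
- another dated record on or after Day 28

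**Size, under assumptions.** With d deaths among n patients and k known survivors dropped, the rate is d/(n − k).

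- *Arm sizes.* The total is 220 (section 4.2), and part 1 gave 40 nangibotide and 20 placebo (section 4.3.1). The remaining 220 − 60 = 160 are assumed to split 80:80. This gives 40 + 80 = 120 and 20 + 80 = 100.
- *One example.* Assume 24 deaths in 120: 24/120 = 20.0%. With k = 3, 24/117 = 20.5%, a shift of 0.5 points.
- *Range, one arm only.* Assume mortality of 15% to 35% and k from 1 to 5. The smallest shift is 18/119 = 15.13% against 15% (0.13 points). The largest is 35/95 = 36.84% against 35% (1.84 points).
- *Equal k in both arms, same true rate.* The largest movement is at 35% with k = 5: 42/115 − 35/95 = 36.52% − 36.84% = −0.32 points.
- *Yardstick.* At an assumed 20% in both arms, the 95% half-width for the difference is 1.96 × √(0.2 × 0.8 × (1/120 + 1/100)) = 10.6 points.

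**Could losses differ by arm?** Note 12 of the schedule limits the Day 60 contact, which would supply a step 2 date, to parts 2 and 3. Under the same 80:80 assumption, 40/120 = 33% of nangibotide and 20/100 = 20% of placebo patients lack that contact. The opportunity for misclassification is therefore somewhat unequal, but the documents do not show that it was realised.

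**The case against.** The strongest reply is that the gap is narrow. The investigator's date is not tied to a visit and can carry later evidence of life. Day 28 and Day 60 may be done by telephone (schedule, note 11). A laboratory sample taken at the Day 28 visit belongs to a visit that already counts. Adverse events are collected to Day 28, with only drug-related serious events after that. What can fall through is mainly an unscheduled sample, or an organ-support or event end date entered without a later contact. All of this stands, and it is why the number is probably small. It does not explain listing four further sources under a condition that is effectively never met.

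It can also be said that ranking direct contact above secondary dates is defensible. That would justify preferring contact when sources conflict. It does not justify discarding a later dated record when no contact exists.

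Safeguards exist too. The dichotomy at 6 or below in section 8.1 carries the last status forward, so such a patient stays in as a non-death. Losses are tabulated by arm, and secondary p-values are exploratory (section 4.1). These limit the consequence without correcting the section 8.2 test.

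A reader might go further and infer three things that the documents do not support:
- *That known survivors were in fact dropped.* The text only makes this possible, and no such patient is shown.
- *That the Kaplan-Meier and Cox analyses are censored too early.* Neither section 8.2 nor section 3.3 of the addendum states a censoring date.
- *That the problem is as large or larger at Day 60.* The SAP does say "The same analyses mentioned above (including sensitivity analyses) will be performed at Day 60", but nothing says that visits are missed more often then. No laboratory or organ-support assessment is scheduled after the Day 28 visit, so the wider rule would rescue few patients there.

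**Conclusion.** The point holds as a minor defect in the Day 28 derivation. The fallback is effectively inert in the mITT set, and a patient with dated evidence of life on or after Day 28 can be excluded as lost. That the fallback is never reached is an inference from dosing and the Day 1 schedule; the SAP does not say it.

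Each error raises the affected arm's rate. The assumed example gives 0.5 points for three patients in one arm, small beside a half-width of about 10.6 points. A shift near two points needs five survivors dropped in one arm only at 35% mortality, and nothing in the documents suggests that. The difference between arms is biased mainly if losses are unequal. The mortality range, the death count, the numbers dropped and the 80:80 split are all assumptions. The primary endpoint is unaffected, because it uses the last available clinical status.

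**What to change.** When no death date is recorded, define the last known alive date as the maximum over all listed sources: investigator date, visits and status contacts, laboratory samples, end of organ support, end of follow-up if completed, and adverse-event end. Make their use mandatory.

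Use only complete, non-imputed dates. Section 4.1 fills partial stop dates to the end of the month or to 31 December for the medication and adverse-event tables. Using those values here would create survival time that nobody observed.

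The main SAP was approved before unblinding and the addendum was written after it, so this cannot be presented as prespecified. Report it as a re-derivation or sensitivity analysis beside the section 8.2 result, with the number of patients whose class changes in each arm. If none change, one sentence settles the matter. The same definition can serve Day 60, although the gain there will be slight. The cost is one sentence of text, a small programming change and one rerun of the mortality tables.

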## 8. Efficacy Analyses

The m-ITT set will be used for all efficacy analyses. Main efficacy analyses may be repeated on the ITT and Per Protocol analysis sets.

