#### **Sensitivity analyses:**

Primary sensitivity analysis: these will be performed in overall patients and according to the baseline sTREM-1 level (above or equal to the median vs below).

The treatment effect will be estimated in an ordinal logistic regression on the 7-point ordinal scale adjusting for treatment and baseline clinical status assuming odds proportionality. The odds ratio for treatment effect with its 95% confidence interval and p-value will be estimated in this model.

As the odds proportionality may not hold (the p-value of the test for odds proportionality will be provided), the 7-point ordinal scale will be dichotomized in six binary endpoints :  $\leq$  cutoff vs  $>$  cut-off: 1 vs  $>1$ ,  $\leq 2$  vs  $>2$ ,  $\leq 3$  vs  $>3$ ,  $\leq 4$  vs  $>4$ ,  $\leq 5$  vs  $>5$ ,  $\leq 6$  vs  $>6$  (of

note, the last cut-off corresponds to the analysis of mortality at day D28). For each cutoff, treatment groups will be compared by a Cochran-Mantel-Haenszel test stratified by baseline clinical status (5 or 6). Odds ratios (with their 95% confidence intervals and p-values) will also be provided. 2x2x2 contingency tables (counts and percentages) will be provided for each cut-off.

Other sensitivity analyses: these will be performed in overall patients and according to the baseline sTREM-1 level (above or equal to the median vs below) except for analyses stratified by randomization stage.

- 1) The 7-point ordinal scale will be compared between treatment groups using a Cochran-Mantel-Haenszel test stratified by randomization stage (part 1 stage 1, part 1 stage 2 and part 2) and baseline status (5 vs 6). The Wald test p-value for the difference in raw mean scores will be provided.
- 2) The change in the 7-point ordinal scale from baseline to Day 28 will be categorized in two categories: 'improved', 'not improved'.

The distribution (counts and percentages) of the binary scale will be displayed by treatment group and baseline level (5 or 6) (i.e., the 2x2x2 contingency table).

The treatment groups will be compared by a Cochran-Mantel-Haenszel test stratified by baseline clinical status (5 or 6). The odds ratio (with its 95% confidence interval and p-values) will also be provided.

- 3) The change in the 7-point ordinal scale from baseline to Day 28 will be categorized in three categories: 'improved', 'unchanged', 'worsened'.

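### The known-status mortality rule in SAP 8.2 keeps documented deaths but drops uncontacted survivors: probably a small error at Day 28, but a structural one at Day 60, where part 1 patients have no planned visit

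*SAP*

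**What the plan says.** SAP section 8.2 sets the mortality comparison on patients with known status: "Inferential analysis will be based on patients which status (alive or dead) is known at Day 28 (i.e. excluding patient lost to follow-up before Day" […]. It adds "Missing data will not be imputed". Loss is defined as follows: "Any patient with last date known to be alive < Day 28 without death information will be considered lost to follow-up in this summary". The last-alive date is the latest of several sources, including the investigator's own entry and any documented Day 28 or Day 60 status. Deaths count over a slightly longer window: "any death occurring between the start of study drug infusion and the start of study drug infusion + 30 days". The estimate is a Mantel-Haenszel risk difference, stratified by baseline clinical status 5 or 6, with a 95% CI.

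Section 8 says "The m-ITT set will be used for all efficacy analyses".

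Among the sensitivity analyses of 8.2, "Kaplan-Meier estimates of mortality will also be estimated at Day 28". Item 3 there repeats all the mortality analyses at Day 60. In the schedule (section 11.1), footnote 12 to the Day 60 column limits that contact to patients in parts 2 and 3.

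In section 8.1 a patient with missing Day 28 status and no documented death by Day 28 keeps the last available status. The same patient therefore counts as not dead in the cut at 6 or below versus above 6. Of that cut the SAP says "note, the last cut-off corresponds to the analysis of mortality at day D28".

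The addendum (section 3.3) adds a stratified log-rank test, a Cox hazard ratio and survival curves at both days.

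**The concern.** Inclusion in the mortality test depends partly on the outcome. A patient who dies on Day 10 is counted. A patient last seen alive on Day 10 and never heard of again is removed from both numerator and denominator, and the days observed alive are discarded. The resulting rate is the risk of death among patients with known status, which need not equal mortality in the mITT set.

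Day 28 mortality is the key secondary endpoint, and its risk difference and interval will be read even though its p-value is exploratory. No analysis the SAP commits to gives a censoring-based risk difference with an interval, or a worst-case bound for lost patients. At Day 60 the exclusion no longer depends on chance loss. It follows from the visit plan, in the part of the trial with unequal allocation.

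**Working it through.** **Inputs from the SAP.** 220 patients (4.2). Part 1 gave 40 nangibotide and 20 placebo; part 2 is 1:1 (4.3.1). The remaining 160 patients split about 80:80, so about 120:100 overall. The SAP states no mortality rate, loss rate or power for mortality, so there is no figure to reproduce, and every rate below is an assumption.

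**Day 28, one arm.** Let p be true mortality, qs the share of survivors lost and qd the share of decedents lost before their death is recorded. The known-status rate is

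p(1−qd) / [p(1−qd) + (1−p)(1−qs)].

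It exceeds p exactly when qs > qd. With qd = 0 the bias in percentage points is:

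| p | 2% lost | 5% lost | 10% lost | 15% lost |
|---|---|---|---|---|
| 15% | +0.26 | +0.67 | +1.39 | +2.19 |
| 25% | +0.38 | +0.97 | +2.03 | +3.17 |
| 35% | +0.46 | +1.18 | +2.43 | +3.78 |

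The direction is not fixed. With p = 25%, qs = 10% and qd = 20%, the rate is 0.200/(0.200 + 0.675) = 22.9%, a bias of −2.14 points.

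**Day 28, between arms.** Assume true mortality of 30% on placebo and 22% on nangibotide (difference −8.0 points), with only survivors lost. The Kaplan-Meier column comes from a simulation with 400,000 patients per arm, truncated-exponential death times, and lost survivors censored uniformly over Days 8–27.

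| Survivors lost, placebo / nangibotide | Placebo rate | Nangibotide rate | Known-status difference | Kaplan-Meier difference |
|---|---|---|---|---|
| 5% / 5% | 31.1% | 22.9% | −8.2 | −8.0 |
| 3% / 8% | 30.6% | 23.5% | −7.2 | −7.75 |
| 8% / 3% | 31.8% | 22.5% | −9.25 | −8.4 |
| 5% / 15% | 31.1% | 24.9% | −6.2 | −7.55 |

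The known-status errors are 0.2 to 1.8 points. In the three unequal-loss rows Kaplan-Meier removes roughly two-thirds to three-quarters of the error, not all of it.

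For scale, the standard error of the difference is √(0.22×0.78/120 + 0.30×0.70/100) = 0.059. The 95% half-width is therefore about 11.6 points. In a separate simulation with equal true mortality of 25%, losing 10% versus 2% of survivors moved the two-sided 5% type I error from about 5.1% to 5.9%.

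**Day 60.** Let n1 be the arm's part 1 patients (40 or 20), r the share of part 1 deaths recorded and s the share of part 1 survivors with a contact at or after Day 60. Assume part 2 is fully followed. The known-status rate is

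p(80 + r·n1) / [80 + r·p·n1 + s(1−p)·n1].

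It equals p when r = s. With r = 1 and s = 0:

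| True mortality, both arms | Nangibotide | Placebo | Spurious difference |
|---|---|---|---|
| 15% | 18/86 = 20.9% | 15/83 = 18.1% | +2.9 |
| 25% | 30/90 = 33.3% | 25/85 = 29.4% | +3.9 |
| 35% | 42/94 = 44.7% | 35/87 = 40.2% | +4.5 |

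These are crude, unstratified differences, and r = 1 with s = 0 is the extreme case. Part 1 deaths up to Day 28 fall within planned follow-up, so r should be well above zero. The artefact shrinks as s rises towards r.

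**8.1 against 8.2.** A patient lost alive is in the denominator of the cut at 6 or below versus above 6, counted as alive, but is absent from 8.2. The imputation rule in 8.1 also looks at deaths to Day 28, whereas 8.2 counts deaths to study day 31. The two analyses therefore need not agree.

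**The case against.** A reader might infer that anyone who leaves early without a recorded death is dropped. The SAP does not say so. Any later evidence of being alive, including at Day 60, restores the patient, and the schedule allows Day 28 and Day 60 contact by telephone. This stands, and it should keep Day 28 loss low.

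A reader might also infer that the rule always overstates mortality, or works against nangibotide at Day 28. Nothing in the SAP shows who is lost or from which arm, and the direction reverses if decedents are lost more often.

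Much of the remedy is already planned: losses tabulated by arm, Kaplan-Meier at both days, log-rank and Cox analyses, and in effect an all-lost-alive run through the 8.1 cut, though with an odds ratio and not a risk difference. Tipping-point analyses and multiple imputation are permitted but optional and post hoc. Naming the mITT set does not by itself fix missing-data handling, and the note in 8.1 can be read as saying only that category 7 means death. Kaplan-Meier is itself imperfect if recovered patients are the ones lost. Replacing the headline estimator after unblinding would be a post hoc choice. These points rule out calling the Day 28 test invalid or demoting it.

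They do not answer Day 60. Section 3.2 mentions a Day 60 visit without restricting it by part, so some part 1 patients may have been contacted, but footnote 12 is explicit. The sensitivity analysis stratified by randomization stage would remove the artefact: with r = 1 and s = 0, every part 1 patient counted is dead in both arms. The main Day 60 comparison has no such stratification.

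**Conclusion.** The point holds in limited form. At Day 28 the complete-case rule is a weakness of the main mortality estimate. Its likely size is under about 1 point for a few percent loss and about 1 to 2 points under marked imbalance between arms, against a half-width of about 11.6 points. The sign depends on who is lost. The stronger conclusion, that the Day 28 result is materially biased in a known direction, is not supported.

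At Day 60 the rule is structurally wrong for part 1. Under equal true mortality of 15% to 35%, all part 1 deaths recorded and no part 1 survivor contacted, it creates a difference of about 3 to 4.5 points against nangibotide. Partial contact with part 1 survivors, or incomplete recording of part 1 deaths, would reduce this.

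**What to change.** - **Day 28:** keep the pre-specified known-status result. Beside it, labelled as added after unblinding, report the Kaplan-Meier risk difference on all mITT patients, censored at the last known alive date and combined over baseline status 5 and 6, with a 95% CI. Add all-lost-alive and all-lost-dead bounds on the risk-difference scale. State the horizon at which Kaplan-Meier is read, since 8.2 counts deaths to study day 31.
- **Day 60:** use the Kaplan-Meier difference, or restrict the known-status analysis to part 2 patients. If Kaplan-Meier is used, censor part 1 patients at their Day 28 end of study whether or not a later death is known. Otherwise the same asymmetry returns. Report how many part 1 patients have Day 60 information, by arm and vital status.
- **Section 8.1:** state that the cut at 6 or below versus above 6 carries lost patients forward as alive and so uses a different denominator from 8.2.

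The cost is a few extra analyses on dates already derived in 8.2. Kaplan-Meier still assumes non-informative censoring, which is why the bounds are needed.

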### **Sensitivity analysis :**

- 1) The mortality rate at Day 28 will be compared between treatment group using a CMH adjusted for baseline clinical status (5 vs 6) and randomization stage (part 1 stage 1, part 1 stage 2 and part 2). The adjusted difference in mortality rates between nangibotide and placebo (nangibotide ACM28 rate - placebo ACM28 rate) will be estimated with its 95% confidence interval using Mantel-Haenszel method.

- 2) Kaplan-Meier estimates of mortality will also be estimated at Day 28. The same analysis will be conducted in patients with a sTREM-1 above vs below the median value at baseline.
- 3) The same analyses mentioned above (including sensitivity analyses) will be performed at Day 60.

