#### 3.2. Treatments

In all parts of the study, the intervention will remain the same.

Patients will receive a continuous intravenous (i.v.) infusion of nangibotide at 1.0 mg/kg/h or a matching placebo. Treatment with study drug must be initiated as early as possible but no later than 48 hours after the initiation of ventilatory support. Patients will be treated for 5 days or until discharge from critical care, whichever is sooner. The treatment with study drug will be in addition to standard of care. Follow-up visits will be performed on days 8 and 14. The end of study visit is at Day 28. A further follow up visit will be undertaken on day 60.

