## 4. General Statistical Considerations

### 4.1. Tabulations and Presentations

All summaries and results in Tables, Listings and Figures (TLFs) should be presented for the following treatment groups:

| Treatment groups                                                  | Label in TLFs           |
|-------------------------------------------------------------------|-------------------------|
| 1.0 mg/kg/h continuous intravenous (i.v.) infusion of nangibotide | Nangibotide 1.0 mg/kg/h |
| Matching placebo                                                  | Placebo                 |

Continuous data will be described using descriptive statistics (i.e. n, mean, standard deviation, median, interquartile range (IQR), minimum, and maximum). Categorical data will be described using the patient count and percentage in each category. For the summary statistics of all numerical variables unless otherwise specified, minimum and maximum will be displayed to the same level of precision as reported. Mean, median and IQR will be displayed to one level of precision greater than the data collected. Standard deviation will be displayed to two levels of precision greater than the data collected.

When count data are presented, the percentage will be suppressed when the count is zero in order to draw attention to the non-zero counts. A row denoted “Missing” will be included in count tabulations where specified on the shells to account for dropouts and missing values. The denominator for all percentages will be the number of patients in that treatment within

the Analysis Set of interest, unless otherwise specified. Percentages will be presented to one decimal place.

Any imputed data will be used in summary tables and figures and the original collected data will be displayed in listings. Data will be displayed in all listings sorted by treatment group. Patients will be identified in the listings by the patient identification number concatenated with the investigator number.

Two-sided p-values will be displayed except for the primary analysis of clinical status (7-point ordinal scale) at Day 28.

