### **8.3.4. Sustained remission**

The number and percentage of patients alive and not hospitalized at Day 60 will be described by treatment overall and by baseline clinical status. Patients withdrawn alive before Day 60 and without any information on survival/hospitalization status on or after Day 60 will be considered as unknown.

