| Discharge letter collection      |                |                 |   |   |   |   |     |          |           | X                       | X                           |
| Quality of Life/Functional assessment        |                |                 |   |   |   |   |     |          |           |                         | X                           |

|                                                             |  |
|-------------------------------------------------------------|--|
| SCR : screening ; EoT: end of treatment; EoS : end of study |  |
|-------------------------------------------------------------|--|

- 1: Days refer to calendar days, day 1 is defined as the calendar day of first study drug administration
- 2: In case of emergency consent, confirmation of consent as soon as patient is capable
- 3: Women of childbearing potential
- 4: Estimate in case measurement is not feasible
- 5: Patients will be treated for 5 days (120 hours) or until ICU discharge, whichever is sooner
- 6: All medication taken within the last 24 hours before start of treatment should be documented. This does include any other study medication from other trials.
- 7: Assessments will be performed before IMP initiation (Day 1) then daily until day 14. Further assessment will be made on day 28 and day 60 even in case patient is discharged from ICU.
- 8: AEs will be collected until day 28
- 9: Discharge letters from ICU discharge (where permissible and possible) at day 28 and day 60
- 10: Before first treatment administration
- 11: Day 28 and Day 60 visit may be completed by site via telephone call if visit to study center not possible.
- 12: By telephone or in person (Patients in part 2 or 3 only)
- 13: Review only of medications reported as ongoing at day 28
- 14: Drug related SAEs only after day 28

[figure not shown]

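### If the Day 60 visit covers only parts 2 and 3, the main Day 60 mortality comparison keeps part 1 deaths, loses part 1 survivors and tilts against nangibotide

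*SAP*

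**What the plan says.** **Day 60 mortality.** SAP 8.2, sensitivity item 3, reads: "The same analyses mentioned above (including sensitivity analyses) will be performed at Day 60". The analyses being repeated are the CMH stratified by baseline clinical status, a CMH that adds "randomization stage (part 1 stage 1, part 1 stage 2 and part 2") as strata, and Kaplan-Meier. Because part 1 stages are named as strata, part 1 is included. Section 8 agrees: "The m-ITT set will be used for all efficacy analyses", with no restriction by part.

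**Unknown status.** Section 8.2 states: "Inferential analysis will be based on patients which status (alive or dead) is known at Day 28". A patient last known alive before the cut-off day, with no death information, counts as lost to follow-up and is left out. Nothing is imputed.

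**Who has a Day 60 visit.** Footnote 12, attached to the Day 60 column in section 11.1, reads: "By telephone or in person (Patients in part 2 or 3 only"). Section 3.2 says only: "A further follow up visit will be undertaken on day 60". Footnote 7 also places assessments on Day 60 without a limit by part.

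**Day 60 percentages.** Section 8.3.4 says: "Patients withdrawn alive before Day 60 and without any information on survival/hospitalization status on or after Day 60 will be considered as unknown". Section 8.3.5 has a parallel rule. Under section 4.1, "The denominator for all percentages will be the number of patients in that treatment within" the analysis set, unless another denominator is specified.

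**The concern.** A death by Day 28 is still a known status at Day 60. A survivor last seen at the Day 28 visit (window +7 days) is not known at Day 60. If part 1 has no Day 60 contact, the known-status rule therefore selects on outcome within part 1.

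That selection would not favour either arm if part 1 made up the same share of both. It does not: part 1 is 40 of about 120 nangibotide patients (33%) but 20 of about 100 placebo patients (20%). Mortality is inflated in both arms, and more so on nangibotide.

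All-cause mortality, sustained improvement, and being alive and free of respiratory support, each at Day 60, are listed secondary endpoints (section 3.3.2). Section 8.4 also allows Day 60 outcomes to inform the choice of the sTREM-1 cut-off. Exploratory status lowers the stakes but does not remove a bias that the rule itself creates.

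**Working it through.** **Inputs from the SAP.** Section 4.3.1: the first 20 patients at 1:1 give 10:10. The next 40 at 3:1 give 30:10. Part 1 is therefore 40:20. Section 4.2: total 220, so part 2 has 220 − 60 = 160 patients, taken as 80:80 under 1:1 allocation.

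**Check against the SAP's own figure.** Effective size, summing 4ab/(a+b) over stages: 20 + 4·30·10/40 + 160 = 20 + 30 + 160 = 210. This reproduces the ~210 in section 4.1, so the allocation is read correctly.

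**Assumptions.** The SAP gives no mortality rates, so a range is used, equal in both arms (no drug effect). First case: no part 1 survivor has status on or after Day 60. The baseline-status mix is taken as the same in both arms and all parts.

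**Expected Day 60 rate under the known-status rule**, with m28 and m60 the true mortality:

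- nangibotide: (40·m28 + 80·m60) / (40·m28 + 80)
- placebo: (20·m28 + 80·m60) / (20·m28 + 80)

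| m28 / m60 | Nangibotide | Placebo | Difference |
|---|---|---|---|
| 15% / 20% | 22/86 = 25.6% | 19/83 = 22.9% | +2.7 |
| 20% / 25% | 28/88 = 31.8% | 24/84 = 28.6% | +3.2 |
| 25% / 30% | 34/90 = 37.8% | 29/85 = 34.1% | +3.7 |
| 35% / 40% | 46/94 = 48.9% | 39/87 = 44.8% | +4.1 |

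The true difference is 0 in every row, and both arms lie above the true Day 60 rate. In 20,000 simulated trials per scenario, with a pooled two-proportion z test, one-sided rejection towards harm at nominal 2.5% was 5.4% (15%/20%), 6.6% (25%/30%) and 7.4% (35%/40%).

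**If a fraction f of part 1 Day 28 survivors has Day 60 status.** Part 1 then contributes n1·(m28 + f·(m60 − m28)) deaths and n1·f·(1 − m60) survivors. At f = 0.5:

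- 15%/20%: 23/103 = 22.3% v 19.5/91.5 = 21.3%, or +1.0
- 25%/30%: 35/105 = 33.3% v 29.5/92.5 = 31.9%, or +1.4
- 35%/40%: 47/107 = 43.9% v 39.5/93.5 = 42.2%, or +1.7

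At f = 1 the difference is 0.

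**A true 10-point benefit at both days (f = 0).** Placebo 25%/30%: 22/86 − 29/85 = 25.6% − 34.1% = −8.5. Placebo 35%/40%: 34/90 − 39/87 = 37.8% − 44.8% = −7.0.

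**Stage-stratified CMH (f = 0).** Part 1 strata contain only deaths, so their difference is 0, and only part 2 (weight 80·80/160 = 40) carries signal. With placebo 25%/30%, the part 1 weights are 1.5·2.5/4 = 0.94 and 4.5·2.5/7 = 1.61, so −10 becomes −10·40/42.55 = −9.4. With placebo 35%/40% it becomes −9.1. With no effect it gives 0.

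**Kaplan-Meier**, part 1 survivors censored after Day 28: simulated mean difference within 0.04 points of 0.

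**Percentages in 8.3.4 and 8.3.5.** If no part 1 patient counts as an event but all stay in the denominator, a true 60% in both arms shows as 80·0.6/120 = 40% v 80·0.6/100 = 48%. A true 50% shows as 33.3% v 40%, and a true 70% as 46.7% v 56%.

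**The case against.** **The premise is not settled.** A reader might infer from footnote 12 that part 1 certainly had no Day 60 visit. Section 3.2 and footnote 7 state Day 60 assessment without that limit, so the SAP conflicts with itself and the bias is conditional. This stands.

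**Part 1 need not contribute only deaths.** Section 8.2 accepts an investigator-recorded last-alive date, which needs no visit. This also stands, and is why a range is given rather than the worst case alone.

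**Most Day 60 mortality analyses escape.** It is tempting to say that Day 60 results as a whole are biased. They are not. Kaplan-Meier and the log-rank and Cox analyses in Addendum 3.3 can censor part 1 survivors. The stage-stratified CMH is unbiased under no effect and only shrinks a real one. Respiratory support type (8.3.2) already excludes patients who died or were lost before Day 60. What remains is the CMH stratified by baseline status alone.

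**The percentage example is a reading, not a stated rule.** The unknown category in 8.3.4 and 8.3.5 covers patients withdrawn alive, which does not clearly describe part 1 patients who completed Day 28. Section 4.1 allows other denominators. The objection shows that the text is unclear, not that it is safe.

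**The bias is small beside the noise.** At 20%/25% the standard error is √(0.318·0.682/88 + 0.286·0.714/84) ≈ 7 points, against a bias of 3.2. The table of alive, dead and lost patients by arm would expose unequal loss. That is fair, but seeing the imbalance does not correct the estimate.

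**Conclusion.** The concern holds in a limited form. Section 8.2 carries a known-status rule to Day 60 in a set that includes part 1, while footnote 12 gives part 1 no Day 60 visit and nothing in the SAP says how part 1 is then handled. If footnote 12 holds, the baseline-status CMH is biased against nangibotide by about +2.7 to +4.1 points under no effect when no part 1 survivor has later status, by +1.0 to +1.7 when half do, and by nothing when all do. It also overstates mortality in both arms. These figures rest on assumed mortality, an 80:80 split in part 2 and equal baseline mix. The percentages in 8.3.4 and 8.3.5 can be off by about 7 to 9 points if part 1 stays in the denominator with no events.

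Severity is moderate. Section 4.1 makes every p-value other than the primary one exploratory, and the Day 28 primary and key secondary analyses are untouched. Nothing here supports reading the Day 28 conclusions as compromised.

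**What to change.** 1. Reconcile footnote 12 with section 3.2 and footnote 7, so that it is clear which patients had a Day 60 assessment.
2. If footnote 12 holds, restrict the Day 60 mortality CMH, Day 60 clinical status (listed in 3.3.2, while the rules in 8.1 are written for Day 28) and the Day 60 percentages in 8.3.4 and 8.3.5 to part 2 patients, in numerator and denominator. Under no effect the expected difference is then 0, and a true −10 points is recovered as −10.
3. For survival to Day 60 in all patients, rely on the Kaplan-Meier, stratified log-rank and Cox analyses already planned, and state that part 1 survivors are censored at last contact.

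The cost is a few sentences and a population flag. The downside is that Day 60 rates rest on about 160 patients; if footnote 12 is right, those are the only patients with a scheduled Day 60 visit.
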